### Blinding

The study is to be conducted as a double-blind, randomized controlled trial as mentioned above. The participants will be blinded to the treatment group to which they are randomized. They will not be informed whether they will be prescribed topiramate, which is the intervention, or the physically similar starch tablet, which is the placebo medication. The physicians will also be blinded to the study arms. The medication will be prescribed under codes specific for each patient.

### Assessment of capacity and informed consent

When the patient visits the clinic, a senior registrar in psychiatry will approach them and provide information regarding the study. Then the patient will be provided with the information sheet in a preferred language. Next, the patient will be given an opportunity to ask questions about the study. Following this, the patient will be accompanied by a research assistant to visit the external consultant psychiatrist in a separate room to assess the patient’s capacity to provide informed consent to participate in the study. If the capacity is decided to be present, the patient will be given the consent form to provide written informed consent.

### Data collection

Subsequently, using an interviewer-administered questionnaire, a senior registrar in psychiatry will gather preliminary information from the participant and direct the participant to a research assistant. The research assistant is a medical doctor specifically trained in obtaining anthropometric measurements from an adult patient. The research assistant will obtain the measurements mentioned in the data record form and will record the initial assessment details. The anthropometric measurements will include height, waist circumference, body weight, and skinfold thickness. In addition, a detailed assessment of eating patterns, daily energy intake, and physical exercise will be conducted. Afterward, the participant will be assessed by a consultant psychiatrist of the research team using the Brief Psychiatric Rating Scale (BPRS), and the symptom score will be recorded [30]. The anthropometric and clinical assessments are to be carried out in the same manner in every monthly visit during the 3-month study period. Details on the age of onset of the disorder, number of relapses, past and current treatments, and the presence of medical disorders will be gathered from the patients and, if necessary, from their relatives for clarification, as well as from the clinic records and past diagnosis cards.

### Intervention

After the clinical assessment is completed, the research assistant will accompany the participant to the randomization room, where the above-mentioned independent person will provide the participant with a code number, which will signify his or her group. Subsequent to this, the participant will be assessed, and the usual medication will be written on the clinic prescription card by medical doctors independent of the research team. Other medications, including antipsychotics, will be continued independent of the study. The participant will be given a prescription according to the predefined dosage under a specific code for the individual patient.

The study group is to be commenced on oral topiramate 25 mg once nightly at the beginning. The dosage is to be titrated up every 2 weeks by 25–50 mg, depending on the tolerability. The targeted level is 100 mg daily in twice-daily doses. Participants in both groups are planned to be screened for any adverse effects pertaining to topiramate therapy. The control group will be provided with a placebo containing starch as a pill that is similar in appearance to the topiramate pill. A number of tablets provided will match the usual tablet count of the intervention group. Adherence is to be monitored via daily medication intake records maintained by the patient and/or a family member. At the end of the study period, each participant and the relevant physician are to be informed of the medication prescribed. After being explained the benefits and drawbacks of continuing topiramate, the patient will be allowed to decide on further topiramate therapy.

All participants are to be informed of adverse effects of topiramate, regardless of their treatment arm, as well as of what measures are to be taken if side effects occur. This medication will be recorded in written form in a separate, closed file, and the medication is to be handed to the participant over a special counter at the hospital dispensary. The medications will be coded specifically so that the physicians involved in the study are unaware of the prescription during the study process.

### Study outcomes

The primary outcome of the study is changes from baseline values in body weight, waist circumference, and/or skinfold thickness (or BMI) at three follow-up time points. The points of measurement are after the first, second, and third months of the trial period. The secondary outcome is the change in the symptom score according to the BPRS assessed at three follow-up time points. The symptom scores are assessed only to determine a possible exacerbation of symptoms, even though worsening with topiramate has not been reported in the past.

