**Methods/design:**

Ninety patients with schizophrenia presenting to the Colombo North Teaching Hospital will be randomized to intervention and control groups equally using permuted block randomization. Patients with comorbid metabolic disorders and taking prescribed weight-controlling medications will be excluded. The intervention group will be prescribed topiramate in addition to their antipsychotics in a predefined dosing regimen targeting a dose of 100 mg per day. The control subjects are to receive a placebo. As the primary outcome, anthropometric measurements including weight, waist circumference, skinfold thickness, and body mass index will be recorded at baseline and monthly during the study period of 3 months. The secondary outcome is the change in symptoms according to the clinician-administered Brief Psychiatric Rating Scale. Assessment of capacity will be performed and informed consent obtained from all subjects. Ethics approval has been obtained from the ethical review committee of the Faculty of Medicine, University of Kelaniya, and the trial has been registered in the Sri Lanka Clinical Trials Registry.

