### Sample size estimation

Regarding the sample size calculations, in a previous randomized, double-blind, placebo-controlled trial on topiramate use for schizophrenia to alter weight, the mean reduction of weight in the topiramate group was 1.27 ± 2.28 kg. That study recruited 72 patients who were randomized to study and control groups [11]. The researchers in that study found a significant difference in weight change between the groups during a 12-week period. In addition, there was also a significant improvement in the symptom scores of patients with schizophrenia in the above-mentioned trial. The present study is also a randomized, placebo-controlled trial being conducted over a 12-week period. Therefore, we assume that a similar number of participants at the analysis stage, after excluding the dropouts, will be adequate to obtain a significant result for both primary and secondary outcomes, which are described below. On the basis of these facts, we decided to recruit 90 participants for the study, 45 in each group, considering a possible 20% dropout rate during the 3-month period of the assessment.

Another sample size calculation was done using OpenEpi software for studies comparing two means. The inserted values were 95% CI, 80% power, 1:1 ratio of sample sizes between groups, and mean difference of 2.75 kg derived from a meta-analysis of randomized controlled trials on topiramate adjuvant therapy for schizophrenia [14]. The calculated sample size was 40 for each group, which was below the planned sample size calculated using the previous method. We are aiming to obtain a sample size of at least 100, with 50 in each group.

The sample size was determined by targeting the primary outcome of change in weight of patients with schizophrenia. Whether the secondary outcome of change in symptom scores is fulfilled is not essential to achieving the primary goal of the project, because the symptom score assessment is done only to see if there is a possible exacerbation of symptoms due to the addition of topiramate.

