### Data management

The data collected will be entered using Excel software (Microsoft, Redmond, WA, USA) and will be analyzed using OpenEpi software. At the end of the study period, calculations of mean weight differences (primary outcome) and BPRS symptom scores (secondary outcome) will be done at each assessment time point. The means will be compared for differences using independent *t* tests, and other relevant statistical analyses will be carried out.

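### The protocol gives two different primary outcomes (several unranked body measures, or weight alone) and names no decisive visit, so the false-positive rate exceeds 5% on either reading

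*Protocol article*

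**What the plan says.** Four places in the protocol article describe the primary outcome, and they fall into two pairs.

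**Several measures.** Study outcomes defines it as "changes from baseline values in body weight, waist circumference, and/or skinfold thickness (or BMI) at three follow-up time points" and adds: "The points of measurement are after the first, second, and third months of the trial period". The Methods/design paragraph of the abstract reads: "As the primary outcome, anthropometric measurements including weight, waist circumference, skinfold thickness, and body mass index will be recorded at baseline and monthly". Neither ranks the measures or the visits.

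**Weight alone.** Sample size estimation states: "The sample size was determined by targeting the primary outcome of change in weight of patients with schizophrenia". Data management says that "calculations of mean weight differences (primary outcome) and BPRS symptom scores (secondary outcome) will be done at each assessment time point", and then: "The means will be compared for differences using independent" t tests, with other analyses left open. It names no test for waist circumference, skinfold thickness or BMI.

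The significance level has to be read from the sample size inputs, "95% CI, 80% power, 1:1 ratio of sample sizes between groups, and mean difference of 2.75 kg", which imply 5%. Sidedness is not stated, and two-sided is assumed here. No adjustment for multiple tests is described.

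**The concern.** A trial needs one comparison that decides its question, chosen before the data are seen. Here the sections disagree on which measure that is, and none says which visit.

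The and/or wording, with BMI as an alternative, leaves the choice of measure open. Under Study outcomes, a difference in waist circumference at month 2 could be reported as a primary success while weight at month 3 showed nothing. Even if weight is taken as the only primary measure, three visits give three chances at an unadjusted 5%.

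The sample size reasoning concerns weight and gives no support for a claim on waist or skinfold.

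**Working it through.** **1. The plan's own figure.** The protocol states no overall error rate, so there is none to reproduce. Its total sample size does reproduce: 72 analysable patients inflated for 20% dropout is 72 / (1 − 0.20) = 90. The 72 comes from an earlier 12-week trial cited for its weight change. The sizing is therefore tied to weight.

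**2. Counting the tests.**
- Data management reading: weight at 3 visits = 3 tests.
- Study outcomes reading: 4 measures × 3 visits = 12 tests. Adult height is fixed, so BMI change is weight change divided by a constant for each patient and nearly duplicates it. That leaves about 3 × 3 = 9 distinct tests.

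**3. Independence bound.** For k independent tests at 5%, the chance of at least one false positive is 1 − 0.95^k:
- k = 3: 1 − 0.8574 = 14.3%
- k = 9: 1 − 0.6302 = 37.0%
- k = 12: 1 − 0.5404 = 46.0%

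**4. Allowing for correlation.** Repeated measures on the same patients are correlated, which lowers these figures. The protocol gives no correlations, so those below are assumptions. The method was to draw 400,000 sets of correlated standard normal statistics under no treatment effect and count the sets in which any |Z| exceeds 1.96. The correlation between two tests is the between-measure value times the between-visit value.

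Weight alone at three visits:

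| Between-visit correlation | Any false positive | Favouring topiramate |
|---|---|---|
| 0.3 | 13.6% | 6.8% |
| 0.5 | 12.6% | 6.3% |
| 0.7 | 11.0% | 5.5% |
| 0.9 | 8.4% | 4.2% |

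Four measures at three visits (12 tests, any one counting). Weight–BMI correlation is 0.97, or 0.99 in the last row:

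| Weight–waist / skinfold with the others | Visits 0.3 | Visits 0.5 | Visits 0.7 | Visits 0.9 |
|---|---|---|---|---|
| 0.3 / 0.2 | 36.7% | 34.3% | 30.3% | 23.7% |
| 0.5 / 0.3 | 35.3% | 32.7% | 28.9% | 22.6% |
| 0.7 / 0.5 | 32.2% | 29.9% | 26.2% | 20.3% |
| 0.8 / 0.7 | 28.7% | 26.5% | 23.2% | 18.0% |
| 0.9 / 0.8 | 25.1% | 22.9% | 20.1% | 15.6% |

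False positives favouring topiramate are about half of each entry, from 7.8% to 19.2% over this grid, against a nominal 2.5%.

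**5. Check with t tests.** Simulating actual two-sample t tests with 36 patients per arm (72 / 2) gives nearly the same results. At 0.7 / 0.5 and between-visit 0.7, the rate is 26.3% for the 12 tests and 10.9% for weight alone.

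**The case against.** The best defence is that weight is clearly the intended lead measure. The Background gives the primary objective as reducing weight, the trial is sized on weight, Data management labels weight as primary, and the Discussion names weight reduction as the ultimate goal. The abstract only says that the measures will be recorded, and sets no testing rule. This makes weight the natural choice. It does not remove the conflict, because the section that defines the outcomes says something else.

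A reader might infer that all four measures are each t-tested as primary and that the false-positive rate is simply 20–30%. The documents do not support that. Data management applies its t tests to weight and the BPRS score only. The higher figures need the Study outcomes wording to be taken as the success rule, together with correlations that the protocol does not give. They also count false positives in both directions.

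A reader might also infer that the sizing already fixes weight at 12 weeks. It does not quite do so: 12 weeks is the length of the earlier trial and of this one, but no visit is given for the 2.75 kg difference.

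Finally, a multiplicity adjustment may properly sit in a statistical analysis plan that is not shown, and its absence here is not the point. The point is that this document states two primary outcomes. A later plan would have to overrule one of them.

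**Conclusion.** The concern holds in this form: the protocol contradicts itself on the primary measure and fixes no decisive visit. That much rests on the text alone.

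The size depends on the reading. With weight at three visits, the chance of at least one false-positive primary result is about 8–14%. If any measure at any visit may count, it is roughly 15–35%, with independence bounds of 37% for 9 distinct tests and 46% for 12. Both readings assume an unadjusted two-sided 5% per test. The ranges come from assumed correlations of 0.3–0.9 between visits and, on the second reading, 0.2–0.9 between measures (weight–BMI 0.97–0.99). Either way the rate is above 5%, so the point should be settled before analysis.

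**What to change.** In the abstract, Study outcomes and Data management, state one primary outcome: change in body weight (kg) from baseline to month 3, compared between groups once at two-sided 5%. Make waist circumference, skinfold thickness, BMI and the month 1 and month 2 comparisons secondary. This matches the weight objective in the Background and the weight-based, 12-week reasoning in Sample size estimation. That section should also name month 3, since it gives no visit now.

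Trial status reports that recruitment began in September 2017. The change should therefore be recorded as a dated amendment made before any unblinded data are seen. The registry entry was not available for this review and should be checked for the same wording.

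The cost is wording and an amendment, with no new data or patients. In return, the trial gives up the option of claiming primary success on waist, skinfold, BMI or an earlier visit.

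### The BPRS is there to look for symptom exacerbation, but a t test for a difference with 36 to 40 per arm cannot exclude a moderate worsening, and the claim that the sample suffices for this outcome has no basis

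*Protocol article*

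**What the plan says.** The Study outcomes section defines the measure: "The secondary outcome is the change in the symptom score according to the BPRS assessed at three follow-up time points". It then limits its purpose: "The symptom scores are assessed only to determine a possible exacerbation of symptoms". The Sample size estimation section repeats the limit: "the symptom score assessment is done only to see if there is a possible exacerbation of symptoms due to the addition of topiramate".

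The Data management section gives the analysis for weight and BPRS alike, at each assessment: "The means will be compared for differences using independent *t* tests, and other relevant statistical analyses will be carried out".

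On numbers, the Sample size estimation section states: "we decided to recruit 90 participants for the study, 45 in each group, considering a possible 20% dropout rate". It later gives an aim of at least 100, 50 per group. It describes an earlier 72-patient trial with a significant weight difference and a significant improvement in symptoms, and assumes that a similar number analysed will be "adequate to obtain a significant result for both primary and secondary outcomes". Its last paragraph says that the size was determined on weight change and that the secondary outcome is not essential to the main goal.

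The Eligibility criteria section removes from the final analysis the data of any participant who is given a new antipsychotic, anticonvulsant, mood stabilizer or antidepressant during the study. The reason given is the effect of such drugs on weight.

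**The concern.** Whether topiramate makes symptoms worse is a question about harm. A t test for a difference can flag a large worsening. If it finds nothing, it leaves the question open unless the confidence interval is narrow enough to exclude a worsening that matters. The plan names no BPRS effect size, SD or power, yet asserts that the sample is adequate for this outcome.

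The removal rule adds to the problem. Patients whose psychosis worsens are among those most likely to be given a new antipsychotic, so the comparison of BPRS means may lose the very cases it is meant to find.

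What is at stake is how the trial's only named measure of psychotic symptoms is interpreted. The primary weight comparison is not affected.

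**Working it through.** **Number analysed.** The plan's figure reproduces: 72 / (1 − 0.20) = 90 recruited, so 45 × 0.80 = 36 per arm. Under the aim of 100, 50 × 0.80 = 40 per arm. The protocol does not say whether the 20% covers patients removed for a new drug. If it does not, fewer remain.

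**Scale.** The document gives no SD for BPRS change, so the results are in SD units. Assumptions: a common SD in both arms and a two-sided 5% level. The sidedness of the BPRS test is not stated; the 5% level matches the 95% used in the weight calculation.

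**Precision.** Half-width of the 95% interval = t(0.975; 2n − 2) × √(2/n).
- n = 36: 1.994 × 0.2357 = 0.47 SD
- n = 40: 1.991 × 0.2236 = 0.45 SD

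**Power for a true worsening of d SD.** Noncentral t with 2n − 2 degrees of freedom and noncentrality d × √(n/2). For d = 0.5 the noncentrality is 0.5 × 4.243 = 2.12 (n = 36) or 0.5 × 4.472 = 2.24 (n = 40).

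| True worsening | 36 per arm | 40 per arm |
|---|---|---|
| 0.2 SD | 13% | 14% |
| 0.3 SD | 24% | 26% |
| 0.4 SD | 39% | 42% |
| 0.5 SD | 55% | 60% |

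The difference detectable with 80% power, by the normal approximation (1.960 + 0.842) × √(2/n), is 0.66 SD and 0.63 SD. A one-sided 5% test would raise the 0.5 SD power only to 68% and 72%.

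**What a null result allows (36 per arm).** With an observed difference of zero, the interval runs from −0.47 to +0.47 SD. With an observed worsening of 0.3 SD, still non-significant because 0.3 < 0.47, the upper limit is 0.3 + 0.47 = 0.77 SD.

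**What it would take to exclude 0.5 SD.** This value is illustrative. With a true difference of zero, one-sided 2.5% and 80% power, n = 2 × (1.960 + 0.842)² / 0.5² = 62.8, so 63 per arm analysed. Recruitment would be 126 / 0.80 = 157.5, so 158.

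**The adequacy claim.** Three statements in the Sample size estimation section stand side by side:
1. The number is sufficient for significance on the secondary outcome.
2. The ground for this is an earlier trial of similar size that found symptoms improved.
3. The size was set on weight, and the BPRS is there only to look for exacerbation.

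The second says nothing about the ability to detect or exclude worsening. The third undercuts the first: for an outcome kept only to look for harm, reaching significance is not the aim, and no BPRS figure was used.

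**The case against.** A reader might infer that the BPRS is meant to rule out exacerbation and that the trial will declare topiramate safe if p > 0.05. The documents do not support that. They speak of determining or seeing whether exacerbation occurs, which is detection, and a difference test is a coherent, if weak, tool for detection. No rule says that a null result will be taken as safety. That risk of misreading follows from the outcome's single purpose; it is not a stated decision.

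A secondary outcome need not be powered, and the protocol says that this one is not essential. A numerical worsening threshold could sit in a statistical analysis plan that is not shown, so its absence alone is no finding. The Data management section also leaves room for other analyses. Individual deteriorations have other routes of capture: screening for adverse effects (Intervention), reporting of psychotropic changes to the researchers (Ethical aspects), and the rules on serious or intolerable effects (Adverse effects).

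All of this stands and narrows the point. It does not rescue the adequacy claim, which the protocol makes itself and does not support. Nor does it change the arithmetic on what a null result can show. The other routes of capture do not undo the removal rule, which as written applies to the final analysis without limiting it to weight.

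**Conclusion.** The concern holds in a limited form. The named BPRS analysis is not sized for the purpose the protocol gives it. At 36 per arm the 95% half-width is about 0.47 SD and power for a 0.5 SD worsening about 55%; at 40 per arm, about 0.45 SD and 60%. A non-significant result cannot exclude a moderate worsening. The statement that the sample is adequate for the secondary outcome is unsupported and conflicts with the account of how the size was set.

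The figures rest on a common SD, a two-sided 5% level and 20% loss. The 0.5 SD value is a yardstick, not a claim about what matters clinically. How far the removal rule would bias the comparison cannot be computed from the document; the direction of the risk is to hide worsening. The correction is worth making because it is cheap.

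**What to change.** 1. In Sample size estimation, delete the adequacy claim for the secondary outcome, or restate it: the size was set on weight, and no power is claimed for the BPRS.
2. In Data management, report the between-arm difference in BPRS change at month 3 with its 95% confidence interval. State that a non-significant result will not be taken as absence of exacerbation, and that worsening is called excluded only if the interval excludes a threshold set in advance by the investigators.
3. Restrict the removal rule in Eligibility criteria so that it does not apply to the BPRS. Keep participants given a new psychotropic in that analysis.
4. Report per arm the number with a new or changed psychotropic, and the number who withdrew for worsening.

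Cost: wording and one clinical judgement on the threshold. No new data are needed: BPRS is already scored monthly, psychotropic changes are already reported to the researchers, and the Adverse effects section already uses reasons for withdrawal. The conclusion will be more cautious. If topiramate truly had no effect on symptoms, the interval would exclude a worsening of 0.5 SD only about 56% of the time with 36 per arm and 61% with 40 (normal approximation), so a finding of not excluded would be common.
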